**2.11 What is the proposed sample size?**

For this pilot study, a sample of 100 participants will be adequate to evaluate the feasibility criteria.

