Unfortunately, clinicians in many parts of the world do not have ready access to rapid, reliable diagnostics that can provide a microbiologic (aetiologic) diagnosis for acute gastroenteritis. Consequently, cases of diarrhoea without blood are presumed to be viral, and current World Health Organization guidelines recommend against empiric antimicrobial therapy for cases of uncomplicated acute gastroenteritis([8](#_ENREF_8)). In contrast, if there is bloody stools (dysentery), the likelihood that the diarrhoea is caused by a treatable pathogen increases substantially; current WHO guidelines suggest empiric therapy for dysentery using antibacterials targeted against *Shigella* spp., widely assumed to be the most common severe cause of bacillary dysentery ([12](#_ENREF_12)). The problem with this approach is that in many regions the proportion of non-dysenteric diarrhoea caused by treatable bacteria and protozoa may be substantial. Our preliminary results show that in Gaborone, Botswana, in 2011, over 35% of over five hundred children admitted to hospital because of gastroenteritis – most of whom did not have dysentery – were found to be harbouring a treatable enteric pathogen using advanced molecular diagnostic techniques.

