**2.3.3 Delayed swab testing plus probiotic therapy arm.** These participants will be started on *Lactobacillus reuteri* within 24 hours of enrollment. Rectal swabs taken from children in the ‘delayed swab result’ arms will be batched and processed after all enrollment has been completed, and management in hospital will be at the discretion of the attending physician following Princess Marina Hospital standards of care. Should the attending physician consider the diagnosis of bacterial enteritis or cryptosporidiosis based on clinical judgment, azithromycin and/or nitazoxanide will be made available. Probiotic therapy will be continued until the measurement of the primary outcome, 2 months post-enrollment.

**2.3.4 Delayed swab testing plus placebo therapy arm.** These participants will be started on placebo therapy within 24 hours of enrollment and will have rectal swabs resulted only after the conclusion of the study (see 2.3.3). Should the attending physician consider the diagnosis of bacterial enteritis or cryptosporidiosis based on clinical judgment, azithromycin and/or nitazoxanide will be made available. Placebo therapy will be continued until the measurement of the primary outcome, 2 months post-enrollment.

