**2.5 What are the proposed practical arrangements for allocating participants to trial groups?**

A statistician independent of the study will generate a randomization list such that participants can be assigned at random to one of the four study groups in a 1:1:1:1 ratio. The randomization code will be generated by a random number generator and will be blocked (randomly in groups of 4-8), with the random blocking not disclosed. Given the substantial increase in mortality among children with severe acute malnutrition, randomization will be stratified by its presence or absence. Randomization will be communicated to the research assistant using an internet-based system.

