**2.10 What are the *feasibility* outcomes, or criteria for success of this pilot study?**

The specific feasibility criteria of this pilot are:

1) to enroll at least 100 participants during the 12-month study period;

2) to ensure that >95% of participants have a rectal swab taken within 18 hours of admission;

3) to verify that >95% of rectal swabs in the experimental group are resulted within 48 hours of admission;

4) to ensure >95% of participants found to have a treatable enteric pathogen are prescribed appropriate antimicrobials;

5) to ensure that >95% of participants prescribed antimicrobials start them within 24 hours of the test being resulted;

6) to contact >95% of participants 7-14 days after discharge from hospital; and

7) to contact >90% of participants 60 days after admission to hospital.

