**2.12 What is the planned recruitment rate? What is the likely loss to follow-up?**

We are currently refining our novel enteric diagnostics and are enrolling an average of 4 children per day at Princess Marina Hospital, the majority of which would be eligible for the proposed pilot trial. Consequently, it should be possible to enroll all 100 participants within 9 months. In our other studies, we have had extremely good follow-up rates (1 of 60 loss to follow-up at 3 months post-enrollment), so we anticipate having very few (fewer than 5 participants) lost to follow-up in this project. We have budgeted to be able to visit families in their home should they be unable or insufficiently organized to return to Princess Marina Hospital for the final 2-month follow-up visit.

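### One hundred participants are not adequate to evaluate feasibility criteria 4 and 5, which rest on about 17 children and so allow no miss

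*Protocol*

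**What the plan says.** Section 2.11 of the Protocol is a single sentence: "a sample of 100 participants will be adequate to evaluate the feasibility criteria". It gives no denominator, precision target or formula.

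Section 2.10 lists seven feasibility criteria as observed counts or percentages. Two concern the end of the chain from swab to treatment:

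- Criterion 4: "to ensure >95% of participants found to have a treatable enteric pathogen are prescribed appropriate antimicrobials".
- Criterion 5: "to ensure that >95% of participants prescribed antimicrobials start them within 24 hours of the test being resulted".

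Three other passages fix how many children these two criteria can draw on:

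- Section 2.5 has children "assigned at random to one of the four study groups in a 1:1:1:1 ratio", and two of the four groups have rapid testing.
- Section 2.3 says that swabs in the delayed arms "will be batched and processed after all enrollment has been completed".
- Section 1.1 reports a treatable pathogen in "over 35% of over five hundred children admitted to hospital because of gastroenteritis".

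On recruitment, section 2.12 says that current work is "enrolling an average of 4 children per day at Princess Marina Hospital, the majority of which would be eligible", and concludes that "it should be possible to enroll all 100 participants within 9 months".

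**The concern.** The sample size is justified once for all seven criteria, but they do not share a denominator. Criteria 2, 6 and 7 use all participants and criterion 3 uses the rapid-testing arms. Criterion 4 uses only children with a detected pathogen, and criterion 5 only those prescribed antimicrobials. A threshold that is workable with 100 children can become a demand for perfection with fewer than 21.

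Demonstrating feasibility is the stated goal of the pilot (section 1.2), and section 2.15 treats the delay between swab, result and treatment as a prime concern. If the criteria for the last two steps turn on one child, the pilot may label a well-run process a failure, or pass a weaker one by luck.

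There is a smaller, separate matter in section 2.12: the nine-month figure is presented as following from a daily rate that implies much faster recruitment.

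**Working it through.** **The plan's figure.** The 100 cannot be reproduced, because the Protocol gives no expected rate, confidence width, error rate or formula for the feasibility criteria. What can be checked is what 100 yields for each criterion.

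**Denominator for criteria 4 and 5.**
- Inputs: 100 participants (2.11), two of four equal groups with rapid testing (2.5), and 35% positive (1.1, where it is a lower bound).
- Expected rapid-arm positives: 100 × 2/4 × 0.35 = 17.5.
- The 35% comes from 2011 inpatients, some of whom had dysentery, whereas this trial excludes visibly bloody diarrhoea (2.2.2). At an assumed 25% the expected number is 50 × 0.25 = 12.5; at 45% it is 50 × 0.45 = 22.5.
- At 35%, the central 95% range of a binomial with n = 50 is 11 to 24.
- Criterion 5 can have fewer children still, if not every positive child is prescribed treatment.

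**Misses allowed when the rate must exceed 95%.**
- 16/17 = 94.1%, 17/18 = 94.4% and 19/20 = 95.0% all fail.
- 20/21 = 95.2% is the first size at which one miss passes. At 35% positivity the chance of 21 or more positives among 50 is 19%.

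**Chance of meeting criterion 4 or 5 with n = 17.** With no miss allowed this is (true rate)^17:

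| True rate | Chance of meeting the criterion |
|---|---|
| 90% | 0.90^17 = 17% |
| 95% | 0.95^17 = 42% |
| 97% | 0.97^17 = 60% |
| 99% | 0.99^17 = 84% |

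Averaging over the binomial number of positives (n = 50, 35%) changes little: 65% at a true 97% and 21% at a true 90%.

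**Precision.** The exact 95% lower limit for 17/17 is 0.025^(1/17) = 80.5%.

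**The other percentage criteria.**

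| Criterion | Denominator | Misses allowed | Lowest passing result, exact 95% CI |
|---|---|---|---|
| 3 | about 50 | 2 | 48/50: 86.3% to 99.5% |
| 2 and 6 | 100 | 4 | 96/100: 90.1% to 98.9% |
| 7 | 100 | 9 | 91/100: 83.6% to 95.8% |

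**Recruitment rate in 2.12.**
- At 4 children a day, with a majority eligible taken at its floor of 50% (an assumption), there are 2 eligible a day, and 100/2 = 50 days. A true majority gives fewer.
- Nine months is about 274 days, so the plan needs only 100/274 = 0.36 a day.
- Over 12 months, 4 × 0.5 × 365 = 730 eligible children, and 100/730 = 13.7%. At 75% eligible the share is 100/1,095 = 9.1%. Against the whole flow it is 100/1,460 = 6.8%.

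**The case against.** **The criteria are observed percentages.** Section 2.10 sets no confidence bound or test, so intervals apply a standard that the plan does not adopt. This stands in part: the Protocol never promises to prove a rate above 95%. But the no-miss result needs no interval; it follows from the plan's own threshold and numbers. A precision table could also be left to an analysis plan, but section 2.11 itself asserts adequacy.

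**Seventeen is an expected value, not a Protocol figure.** This is fair, and the range is shown above. It does not rescue the claim: more than 20 positives is the less likely outcome at 35%.

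**Criterion 4 does not name the rapid arms.** Read over all 100 children, the denominator is about 35, and one miss would pass (34/35 = 97.1%). But delayed-arm positives become known only after enrolment ends, so a prescription could not follow from the result. The ambiguity itself needs fixing.

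**Stronger readings.** A reader might infer that 100 is inadequate for every criterion. The documents do not support that: criteria 2, 3, 6 and 7 tolerate some misses, and criterion 1 is a count of 100, so it has no bearing on whether 100 is enough.

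A reader might also infer that missing one criterion stops the main trial. Section 2.10 calls these criteria for success and attaches no such consequence.

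Finally, a reader might infer that 2.12 contradicts itself, or that criterion 1 cannot fail. Nine months is a ceiling, the 4 a day comes from a different study, and eligible children need not be consented and randomised. The daily rate and the time limit can both be true; the uptake that connects them is missing.

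**Conclusion.** The adequacy statement in 2.11 is unsupported in general and does not hold for criteria 4 and 5. On the Protocol's own inputs about 17 or 18 children inform them, and one miss fails either criterion at any size up to 20. With 17 children, a site truly at 97% fails each criterion about 40% of the time and a site truly at 90% passes 17% of the time.

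This rests on an even split between rapid and delayed testing, on positivity near 35%, and on reading both criteria as applying to rapid-arm children. If positivity were 45%, the expected number would be 22.5 and one miss would usually be allowed, though the information would still be thin.

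The recruitment point is lesser: an unstated uptake assumption in 2.12, not an error in the sample size.

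**What to change.** 1. **Section 2.11:** limit the adequacy claim. For each criterion give the expected denominator (100, about 50, or about 17) and the exact 95% confidence interval at a plausible result.
2. **Section 2.10:** state that criteria 4 and 5 apply to rapid-arm children with a treatable pathogen. Judge them on the observed count with its exact interval, not on a bare cut-off above 95%.
3. **If the sponsor prefers a count rule,** state how it behaves. At most 1 miss of 17 passes 0.97^17 + 17 × 0.03 × 0.97^16 = 91% of the time at a true 97%, 48% at 90% and 12% at 80%. Such a rule accepts 16/17 = 94.1%, below the present threshold, and passes a site at 90% far more often than the current rule's 17%. That trade-off should be chosen openly.
4. **Section 2.12:** state the uptake assumed between the daily flow and 100 children in nine months, or correct the daily rate.
5. **Criterion 1:** keep the count of 100, and also report the share of age-appropriate gastroenteritis admissions that were enrolled, using the monthly hospital counts already planned in section 3.2.

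None of this needs more participants or a new data source. The cost is that the stated precision will look less favourable, and that the assessment of criteria 4 and 5 changes in substance and should be settled before data are seen.

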**2.12 What is the planned recruitment rate? What is the likely loss to follow-up?**

We are currently refining our novel enteric diagnostics and are enrolling an average of 4 children per day at Princess Marina Hospital, the majority of which would be eligible for the proposed pilot trial. Consequently, it should be possible to enroll all 100 participants within 9 months. In our other studies, we have had extremely good follow-up rates (1 of 60 loss to follow-up at 3 months post-enrollment), so we anticipate having very few (fewer than 5 participants) lost to follow-up in this project. We have budgeted to be able to visit families in their home should they be unable or insufficiently organized to return to Princess Marina Hospital for the final 2-month follow-up visit.

**2.13 What is the proposed type of analysis?**

The principal analysis will be intention-to-treat, i.e. all participants will be analyzed in the groups to which they were randomized, regardless if they received the appropriate antimicrobials (for those in the rapid swab analysis groups) or if they were adherent to the probiotic treatment (for those in the relevant groups). As the primary outcome (mortality) is binary, the chi-square test will be used. The chi-square test will also be used to interpret the following secondary outcomes: presence of stunting at 60-day followup, 7-day mortality, recurrence of acute diarrhoea during the 60-day followup period, re-presentation to a medical professional or readmission to Princess Marina Hospital because of acute diarrhoea in the 60-day followup period, and detectable HIV viral load within 6 months of enrollment. Analysis of covariance or logistic regression will be used to analyze the following secondary outcomes: height z-score at 60 days adjusted for initial height, weight z-score at 60 days adjusted for initial weight, and environmental enteropathy score at 60 days. Survival analysis will be used to analyze the following secondary outcomes: length of stay in hospital, number of days with at least three watery stools, and number of days of fever in hospital. Secondary analyses will attempt to control for the time to initiation of appropriate antimicrobial therapy and the time to initiation of probiotic therapy. Statistical analysis will be conducted using STATA 11.0 (College Station, TX).

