**RESEARCH PROPOSAL**

**1. THE NEED FOR A TRIAL**

**1.1 What is the problem to be addressed?**

Diarrhoeal disease is the second-leading cause of death for children under the age of five ([1](#_ENREF_1)). The majority of these deaths are in lower-income countries; mortality associated with gastroenteritis is rare in North America ([2](#_ENREF_2)). A recent major study including over five thousand children presenting to health centres in sub-Saharan Africa with moderate-to-severe diarrhoea documented an overall mortality of 3.2% ([3](#_ENREF_3)). Unfortunately, the impact of diarrhoea is not limited to mortality; gastroenteritis causes a staggering amount of morbidity as well. A multi-country analysis pooling data from nine large longitudinal studies in lower-income countries showed that both the cumulative diarrhoeal incidence (number of diarrhoeal episodes/year) and the longitudinal diarrhoea prevalence (proportion of days with diarrhoea) were both associated with stunting (height-for-age more than two standard deviations below the mean) ([4](#_ENREF_4)). With every five episodes of diarrhoea, a 13% increase in the odds of stunting at 2 years was observed; the proportion of stunting at age 2 attributable to 5+ diarrhoeal episodes was estimated at 25% ([4](#_ENREF_4)). Stunting, of course, is a critical measure of well-being, as height-for-age at 2 years has been shown to be the best predictor of human capital ([5](#_ENREF_5)). Enteric infections in infants and toddlers have also been associated with cognitive deficits, less attained schooling, less economic productivity, metabolic derangements, and, least surprisingly, lower adult height ([5-7](#_ENREF_5)).

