**2.2 What is the population under study?**

**2.2.1 Inclusion criteria.**

Children aged 3 to 60 months admitted to the Princess Marina Hospital paediatric medical ward primarily because of acute diarrhoeal disease will be eligible. Acute diarrhoeal disease will be defined as at least three watery stools in the 24 hours preceding admission to hospital. Children with HIV infection will not be excluded. Children with severe acute malnutrition will be eligible to be included in the rapid vs delayed testing and targeted treatment arms, but will not be randomized to probiotic (or placebo).

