**2.3 What are the planned trial interventions?**

**2.3.1 All participants.** Data to generate Vesikari scores([20](#_ENREF_20)), a validated measure of gastroenteritis severity, will be collected at enrollment, and all study participants will be weighed and measured using calibrated apparatus. Percent dehydration will be abstracted from the paediatric team admission note (subjective dehydration) and will also be calculated comparing weight nadir in hospital to weight at discharge from hospital (objective dehydration). All participants will have a rectal flocked swab taken at enrollment within 18 hours of admission. Most of these children will not be started on antimicrobials at admission, as per current Princess Marina Hospital and World Health Organization standards, excepting children with severe acute malnutrition. Rehydration procedures will be decided by the attending physician; as per Princess Marina Hospital dehydration protocols, all those with severe dehydration receive intravenous rehydration with isotonic fluids and those with mild-moderate dehydration receive WHO-standard oral rehydration solution (ORS). It is standard of care at Princess Marina Hospital to also provide zinc treatment for gastroenteritis.

**2.3.2 Rapid testing and targeted antimicrobial therapy plus probiotic therapy arm.** These participants will be started on *Lactobacillus reuteri* within 24 hours of enrollment**.** All of these participants’ rectal swabs will be processed using our novel diagnostic techniques and resulted within 48 hours. It will be recommended to the attending physician that *Shigella,* ETEC, and *Campylobacter* infections be treated with azithromycin, and *Cryptosporidium* infections be treated with nitazoxanide. It will also be recommended that antimicrobials will be started as soon as possible, preferably on the day the test results become available, and antimicrobials will be provided free of charge. Probiotic therapy will be continued until the measurement of the primary outcome, 2 months post-enrollment.

**2.3.3 Rapid testing and targeted antimicrobial therapy plus placebo therapy arm.** These participants will be started on placebo therapy within 24 hours of enrollment and will have rectal swabs processed rapidly (see 2.3.2). Placebo therapy will be continued until the measurement of the primary outcome, 2 months post-enrollment.

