**2.8 What are the proposed *clinical* outcome measures?**

**2.8.1 Primary clinical outcome.** The primary outcome is mortality. If the participant dies prior to the 60-day followup, the research assistant will determine the date of death as accurately as possible.

**2.8.2 Other clinical outcomes.** Secondary outcomes will include the following: weight z-score at 60-day followup adjusted for initial weight; height z-score at 60-day followup adjusted for initial height; presence of stunting at 60-day followup; length of stay in hospital; number of days with at least three watery stools; number of days of fever in hospital; 7-day mortality; recurrence of acute diarrhoea during the 60-day followup period; re-presentation to a medical professional because of acute diarrhoea during the 60-day followup period; readmission to a paediatric medical ward during the 60-day followup period; HIV viral load (detectable/undetectable) at the next assessment within 6 months of enrollment, for those participants that are HIV positive; and environmental enteropathy score([21](#_ENREF_21)) (composite of faecal alpha-1 antitrypsin, neopterin, and myeloperoxidase) at 60 days.

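### Day-60 stunting is tested without the enrolment height, the growth covariate is not named as the baseline z-score, and logistic regression is offered for outcomes that are all scores

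*Protocol*

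**What the plan says.** Section 1.2 of the protocol puts stunting at 60 days next to mortality in the research question. Section 2.3.1 provides the baseline: "all study participants will be weighed and measured using calibrated apparatus" at enrolment.

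Section 2.8.2 lists the growth outcomes as "height z-score at 60-day followup adjusted for initial height; presence of stunting at 60-day followup", with a matching entry for weight. Section 2.13 then assigns the methods:

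- Stunting: "The chi-square test will also be used to interpret the following secondary outcomes: presence of stunting at 60-day followup". No baseline term is named.
- Growth z-scores: analysis of covariance or logistic regression for "height z-score at 60 days adjusted for initial height, weight z-score at 60 days adjusted for initial weight". The environmental enteropathy score gets the same pair of methods.

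In both sections the outcome is called a z-score and the covariate is not. Eligibility in 2.2.1 covers "Children aged 3 to 60 months admitted to the Princess Marina Hospital paediatric medical ward". Section 2.5 stratifies randomisation by severe acute malnutrition only. On size, 2.11 says that "a sample of 100 participants will be adequate to evaluate the feasibility criteria"; no power is claimed for growth.

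**The concern.** Height changes slowly, so most children who are stunted at day 60 will already have been stunted at enrolment. A comparison of day-60 stunting that ignores enrolment height treats this persistent between-child variation as noise. The stratification does not balance baseline height-for-age either.

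The wording of the covariate matters for a related reason. Between 3 and 60 months of age, height in centimetres is driven mainly by age, and the z-score outcome has already had age removed. Centimetres would therefore explain little of the outcome, whereas the baseline z-score would explain much of it. Section 2.13 does not say which is meant.

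The model choice is also misassigned. Two z-scores and a composite score are not binary as the protocol defines them, so logistic regression does not fit them. Binary stunting, which it would suit, is given only the chi-square test.

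**Working it through.** The protocol states no alpha, power, SD, stunting rate or baseline-to-day-60 correlation for growth, so there is no planned figure to reproduce. The sizes below rest on assumptions, shown as ranges.

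**Inputs from the protocol.** Ages 3 to 60 months (2.2.1); 100 children allocated 1:1:1:1 in a 2×2 factorial (2.1, 2.5, 2.11), hence about 50 v 50 for the testing comparison. The probiotic comparison is smaller, because children with severe acute malnutrition are not randomised to it. Stunting is height-for-age below −2 SD (1.1).

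**Assumptions.** Height-z SD 1.0–1.6; correlation r between baseline and day-60 height z of 0.70–0.95; approximate height-by-age medians and SDs; two-sided alpha 0.05.

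**Step 1: variance left after adjustment.** With the baseline z-score as covariate, the share left is 1 − r². With height in centimetres it is 1 − c², where c is the correlation of centimetres with day-60 z. In 400,000 simulated children with ages spread evenly over 3–60 months, c was 0.19–0.38. For example, 1 − 0.19² = 0.96.

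| r | cm leaves | cm plus age leaves | baseline z leaves | ratio, cm to baseline z |
|---|---|---|---|---|
| 0.70 | 92–96% | 59–65% | 51% | 1.8–1.9 |
| 0.80 | 89–95% | 46–54% | 36% | 2.5–2.6 |
| 0.90 | 87–94% | 32–42% | 19% | 4.6–4.9 |
| 0.95 | 85–93% | 24–35% | 9.75% | 8.7–9.5 |

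A second run gave 86–97% for centimetres, so the combined range is 85–97%. The outer bounds of the ratio are 0.85/0.51 = 1.7 and 0.97/0.0975 = 9.9, or roughly 1.7 to 10. With a younger age mix centimetres leave 77–94%; if all children were 3–12 months old, 57–87%.

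**Step 2: detectable difference in height z.** At 80% power and 50 v 50, in SD units: (1.960 + 0.842) × √(2/50) × √(share left).

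- Unadjusted: 2.802 × 0.2 = 0.56.
- Centimetres (85–97% left): 0.56 × √0.85 = 0.52 to 0.56 × √0.97 = 0.55.
- Baseline z: 0.40, 0.34, 0.24 and 0.17 at r = 0.70, 0.80, 0.90 and 0.95.

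**Step 3: stunting.** Simulated trials of 50 v 50, mean z −1.0 or −0.5, SD 1.3, true shift 0.3 z, r 0.80–0.95:

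| Analysis | Power |
|---|---|
| Chi-square on day-60 stunting | about 10–13% |
| Stunting adjusted for baseline stunting status | about 11–20% |
| Stunting, logistic regression on baseline height z | about 16–30% |
| Day-60 height z, linear model on baseline z | about 46–96% |

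With mean z −1.0, 66–83% of children stunted at day 60 were already stunted at baseline. With no true effect the chi-square rejected in about 5–6% of trials, so it is valid. The logistic gain is approximate: it falls towards the lower end or a little below when few children are stunted, and the small-sample test can be mildly liberal.

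**What was not computed.** Weight was not simulated. The age argument applies in kind, but enrolment weight is taken in children who may be dehydrated, so the height figures should not be carried over.

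**The case against.** The strongest reply is that nothing in 2.8.2 or 2.13 says centimetres or kilograms. Next to a z-score outcome, initial height may simply be shorthand for the initial height z-score, and a statistical analysis plan could settle it. On that reading the z-score analyses lose nothing. Even on the literal reading, adding age to the model, which the protocol does not rule out, recovers much of the gain. This stands: the covariate is ambiguous, and the loss is conditional.

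It is also fair that these are secondary outcomes in a feasibility pilot and that the chi-square is valid under randomisation. Both limit the weight of the point.

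A reader might infer several stronger claims that the documents do not support:

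- *That the plan discards most of the available precision.* For height z this follows only on the literal reading and at high assumed correlations. For stunting, most of the gap between 10–13% and 46–96% power comes from dichotomising, not from the missing baseline.
- *That the follow-on trial will inherit inflated variances.* Section 1.2 promises data for a sample size, but enrolment and day-60 measurements exist for each child, so SDs and correlations can be computed whichever test is run.
- *That growth is the only informative clinical outcome at this size.* Length of stay and days of diarrhoea are also analysed.

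The objection leaves two things untouched: the stunting test, which is named outright without a baseline term, and the logistic option for the scores.

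**Conclusion.** The point holds as a matter of efficiency and clarity, not bias. Two parts follow from the text alone: the chi-square on day-60 stunting ignores a baseline that is already collected, and logistic regression is offered for outcomes that are all scores. The third part is an ambiguity. Its cost runs from nothing, if initial height is the initial z-score, to a residual variance roughly 1.7 to 10 times larger, if it is centimetres with evenly spread ages and r between 0.70 and 0.95. For stunting the gain from adjustment is modest, from about 10–13% to 16–30% power for an assumed 0.3 z shift. All of these sizes rest on assumed SDs, correlations and age mixes. For secondary outcomes in a pilot of 100 the stakes are limited, but the improvement needs no extra measurement.

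**What to change.** In 2.8.2 and 2.13:

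1. Analyse day-60 height and weight z-scores by linear regression (ANCOVA) on the baseline z-score of the same measure, and name the covariate that way.
2. Analyse day-60 stunting by logistic regression with baseline height-for-age z-score as covariate. State a fallback, either a penalised fit or the chi-square test, if the model separates.
3. Delete the logistic-regression option for the z-scores and the enteropathy score.

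This costs wording only; the enrolment measurements in 2.3.1 suffice. The small downside is that the stunting effect becomes a conditional odds ratio, which is less direct than a difference in proportions, and the model may be unstable if few children are stunted. Reporting the raw proportions by group alongside the model keeps the result easy to read.
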